## **13. ASSESSMENT OF SAFETY**

### **13.1. Assessments**

- Adverse event reporting.
- Concomitant medications.
- Physical Examinations.
- Vital Signs including height and weight.
- Hematology laboratory assessments.
- Chemistry laboratory assessments.
- Pregnancy testing.
- Thyroid function test.

### **13.2. Methods and Timing of Safety Assessments**

#### **13.2.1. Adverse Event Reporting**

All subjects will have AE assessment performed during all visits once the ICF is signed until 28 days after last dose. CTCAE Version 4.0 will be used for grading ([http://ctep.cancer.gov/protocolDevelopment/electronic\\_applications/docs/ctcae4.pdf](http://ctep.cancer.gov/protocolDevelopment/electronic_applications/docs/ctcae4.pdf)).

#### **13.2.2. Concomitant Medications**

All subjects will have concomitant medication and procedure assessment performed at all visits once ICF is signed until 28 days after last dose.

#### **13.2.3. Physical Examinations**

All subjects will have a physical examination at screening, every cycle Day 1 (pre-dose), at treatment discontinuation, and 28 days after last dose. During Cycle 1, physical examination assessments will occur every 7 days.

#### **13.2.4. Vital Signs**

Vital signs (including pulse, blood pressure, and temperature) and weight will be measured at screening, every cycle Day 1 (pre-dose), at treatment discontinuation, and 28 days after last dose. Height will be measured during screening only. During Cycle 1, vital signs will be captured every 7 days.

#### **13.2.5. Hematology Laboratory Assessments**

Hematology laboratory including RBC count, hemoglobin, hematocrit, WBC count and differential (including ANC) and platelet count will be collected at screening, every cycle Day 1 (pre-dose), treatment discontinuation, and 28 days after last dose. During Cycle 1, hematology

laboratory parameters will be collected every 7 days. Hematology assessments may be repeated more frequently if clinically indicated.

#### **13.2.6. Chemistry Laboratory Assessments**

Serum chemistries including sodium, potassium, chloride, CO2, calcium, magnesium, phosphorus, BUN, creatinine, glucose, albumin, total protein, alkaline phosphatase, bilirubin, AST/SGOT, ALT/SGPT, LDH and uric acid will be collected at screening, every cycle Day 1 (pre-dose), treatment discontinuation, and 28 days after last dose. During Cycle 1, chemistry laboratory parameters will be collected every 7 days. Chemistry assessments may be repeated more frequently if clinically indicated.

#### **13.2.7. Pregnancy Testing**

All WCBP who participate in the study will have urine  $\beta$ -HCG levels assessed as a means of pregnancy testing. The subject may not receive investigational product(s) until the investigator has verified that the results of these pregnancy tests are negative (see specifics in Section [21.3](#) or [21.4](#)).

#### **13.2.8. Thyroid Function Test**

Subjects will have free T3, free T4 and total TSH levels analyzed at screening and at treatment discontinuation. Further analysis of free T3, free T4, and total TSH levels will be performed as clinically indicated.

## **14. OTHER ASSESSMENTS**

### **14.1. Biomarker Assessment**

In addition to testing the safety and effectiveness of the investigational product(s), lenalidomide and cetuximab in this study, an exploratory analysis of biomarkers is planned. Celgene Corporation may attempt to utilize existing and/or develop new biomarker assays designed to identify biological and molecular markers which correlate with evidence of the clinical efficacy and/or safety profile of lenalidomide and cetuximab. These analyses may help identify subjects most likely to benefit from lenalidomide and cetuximab.

Biomarker assessment includes, but is not limited to, immuno flow cytometry panel for T cells and NK cells; assessment of cytokines/immune markers (including, but not limited to, IL-6, TGF, IL-8, IL-10, IL-12, IFN- $\gamma$ , and GM-CSF); assessment of growth factors (including, but not limit to, vascular endothelial growth factor [VEGF], soluble VEGF-receptor 2 [sVEGFR-2], phosphorylated VEGFR-2, activated platelet-derived growth factor receptor [PDGFR] and placental growth factor [PGF]); and assessment of circulating tumor cells. Additionally, FC $\gamma$ R, KRAS, and EGFR testing will also be conducted using paraffin tumor.

Biomarkers are objectively measured and evaluated indicators of normal biological processes, pathogenic processes, or pharmacologic responses to a therapeutic intervention. In oncology, there is particular interest in the molecular changes underlying the oncogenic processes that may identify cancer subtypes, stage disease, assess the amount of tumor growth or predict disease progression, metastasis and responses to lenalidomide and cetuximab. These investigations may be useful in developing markers to identify disease subtypes, guide therapy and/or predict disease progression.

#### **14.1.1. Preparation/Handling/Shipping of Tumor and Blood Samples for Biomarker Assessment**

Please refer to the central laboratory manual for detailed instructions on sample handling, labeling and shipment.

##### **14.1.1.1. Plasma**

1. A blood sample will be drawn at Cycle 1 Day 1 (pre-dose), Cycle 2 Day 1, at each tumor assessment, and at treatment discontinuation.
2. The blood will be centrifuged to separate plasma. As much of the plasma as possible is removed with a pipette without disturbing the blood cells and transferred into three vials. Immediately place all 3 tubes vials in a  $-70^{\circ}\text{C}$  freezer.
3. The plasma should be frozen within 60 minutes of collection from the subject. The samples should be shipped on dry ice to central laboratory.

#### **14.1.1.2. Blood for Circulating Tumor Cells**

1. A blood sample will be drawn at Cycle 1 Day 1 (pre-dose), Cycle 2 Day 1, at each tumor assessment, and at treatment discontinuation.
2. Sample is to be maintained at room temperature and mailed overnight to Celgene Corporation for processing.

#### **14.1.1.3. Blood for Immuno Flow Cytometry**

1. A blood sample will be drawn at Cycle 1 Day 1 (pre-dose), Cycle 2 Day 1, at each tumor assessment, and at treatment discontinuation.
2. Sample is to be maintained at room temperature and mailed overnight to central laboratory for processing.

#### **14.1.1.4. Paraffin Blocks or Slides**

Paraffin tumor blocks or approximately 25 unstained slides must be sent for KRAS mutation testing and results reported by central pathology laboratory prior to study enrollment. All paraffin tumor blocks will be shipped back to the clinical site once the slides have been cut.

#### **14.1.2. Sample Storage and Destruction**

These blood and tumor samples and any other components from the cells may be stored for up to 5 years after the end of the study to research scientific questions related to cancer and/or lenalidomide and cetuximab. Celgene Corporation will be the exclusive owner of any data, discoveries or derivative materials from the sample. If a commercial product is developed based on this research project, Celgene Corporation will own the commercial product and the subject will have no commercial rights to such a product and no rights to the data, information, discoveries, or derivative materials gained or produced from the sample.

#### **14.1.3. Confidentiality**

To maximize confidentiality, all biomarker samples and the information associated with the samples will be coded to prevent the exposure of subject's information and identity. Since these evaluations are neither expected to benefit the subject directly nor to alter their treatment course, the results will not be placed in their medical record and will not be made available to members of their family, their personal physician, or other third parties except as specified in the informed consent.

## **15. STATISTICAL CONSIDERATIONS**

This Phase 2 study in pretreated KRAS mutant subjects with metastatic colorectal cancer consists of three parts. Phase 2a – Safety Lead-In part is to explore the dosing of lenalidomide in combination with cetuximab. Phase 2b – POC part is to explore tumor response rate of lenalidomide in combination with cetuximab and lenalidomide alone. Phase 2b – Expansion part will enroll approximately 120 subjects into the recommended regimen from the POC study and further evaluate the response rate of a lenalidomide containing regimen in pretreated KRAS mutant subjects with metastatic colorectal cancer.

### **15.1. Study Population Definitions**

The population for the study CC-5013-COLO-001 will consist of subjects with histologically confirmed KRAS mutant metastatic CRC measurable by RECIST 1.1 who have failed both oxaliplatin and irinotecan-containing regimens, with at least one of the regimens containing bevacizumab. Study population definitions are as follows:

- Intent-to-Treat (ITT) Population – All subjects who take at least one dose of study medication.
- Safety Population – All subjects who take at least one dose of study medication, which is the same as ITT population for this study.
- Efficacy Evaluable (EE) Population – All ITT subjects who meet eligibility criteria, complete at least one treatment cycle of investigational product(s), and have baseline and at least one post-baseline efficacy assessment.

### **15.2. Efficacy Evaluation**

All treated subjects will be included for efficacy analysis. Efficacy will be analyzed once all subjects have withdrawn from the study or completed at least 6 cycles. The hypothesis test for the objective confirmed response rate will be based on the exact binomial distribution Phase 2b – Expansion part. Ninety-five percent confidence intervals will be provided. A descriptive analysis of other evidence of anti-tumor activity will be provided based on clinical, radiographic, and biologic assessments of efficacy. If there are sufficient data, Kaplan-Meier estimates will be provided for duration of response, PFS, DCR, and OS.

Data listings will be provided for all relevant data collected during the studies.

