### Secondary (all phases)

- Progression Free Survival (PFS).
- Safety / Tolerability (type, frequency, severity, and relationship of adverse events to investigational products).
- Duration of Response.
- Disease Control Rate (DCR).
- Overall Survival (OS).

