#### **Efficacy Analysis:**

All treated subjects will be included for efficacy analysis. Efficacy will be analyzed once all subjects have withdrawn from the study or completed at least 6 cycles. The hypothesis test for the objective confirmed response rate will be based on the exact binomial distribution for the Phase 2b – Expansion part. Ninety-five percent confidence intervals will be provided. A case-by-case description of all subjects who exhibited a complete or partial response during the study will be provided. A descriptive analysis of other evidence of anti-tumor activity will be provided based on clinical, radiographic, and biologic assessments of efficacy. If there are sufficient data, Kaplan-Meier estimates will be provided for duration of response, PFS, DCR, and OS.

Data listings will be provided for all relevant data collected during the studies.

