### **7.2. Secondary**

- Progression Free Survival.
- Safety / Tolerability (type, frequency, severity, and relationship of adverse events to investigational products).
- Duration of Response.
- Disease Control Rate.
- Overall Survival.

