#### **12.2.2. Response Assessment**

Tumor response will be evaluated every 2 cycles beginning with Cycle 3 Day 1 and at treatment discontinuation. Response and progression will be evaluated using the RECIST 1.1 criteria ([Eisenhauer, 2009](#)). All subjects with evidence of objective tumor response (CR and PR) should have the response confirmed with repeat assessments performed at the next scheduled scan (every 2 cycles following Day 1 Cycle 1).

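### Section 15.2 and the synopsis assign Kaplan-Meier estimation to the disease control rate, which the protocol names only as a rate and which should be reported as a proportion (minor)

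*Protocol*

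**What the plan says.** - Section 7.2 lists "Disease Control Rate" as a secondary endpoint, and the synopsis lists it for all phases. The abbreviation table (Table 3) expands DCR in the same way. None of these places gives an event, a starting point for time, or a censoring rule.
- Section 15.2 gives the method: "If there are sufficient data, Kaplan-Meier estimates will be provided for duration of response, PFS, DCR, and OS". The efficacy analysis paragraph of the synopsis repeats it: "Kaplan-Meier estimates will be provided for duration of response, PFS, DCR, and OS".
- For the other rate endpoint, Section 15.2 uses a different method: "The hypothesis test for the objective confirmed response rate will be based on the exact binomial distribution". The next sentence, "Ninety-five percent confidence intervals will be provided", follows that test and is not tied to DCR.
- On the population, Section 15.2 says: "All treated subjects will be included for efficacy analysis".
- On timing, Section 12.2.2 says: "Tumor response will be evaluated every 2 cycles beginning with Cycle 3 Day 1 and at treatment discontinuation". Section 12.2.1 and footnote 12 of Table 2 waive the discontinuation scan if one was done within the previous 28 days.

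**The concern.** Kaplan-Meier estimates the probability of remaining event-free as a function of time. It needs an event, an origin and a censoring rule for each subject. A disease control rate has none of these as the protocol names it: each subject either has disease control or does not, and the result is a fraction. Applied literally, the sentence yields a curve, and the protocol names no time at which to read it.

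Two things follow. First, the stated method does not produce the stated secondary endpoint, and no other method is named for it. Second, the opening condition about enough data makes sense for a survival curve but needlessly makes the DCR analysis optional. This is not detail left to the statistical analysis plan. The protocol assigns a method, so a plan that followed it would carry the error forward, and one that corrected it would depart from the protocol.

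**Working it through.** **1. The four endpoints in the sentence.** Duration of response, PFS and OS are times to an event. DCR is the only one of the four named as a rate.

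**2. How the protocol treats its other rates.** Section 15.7 gives an interval of 22% to 39% for a 30% response rate in about 120 subjects. With x = 36 and n = 120, the exact (Clopper-Pearson) limits are

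- lower: 2.5% quantile of Beta(x, n − x + 1) = 21.98%
- upper: 97.5% quantile of Beta(x + 1, n − x) = 39.04%

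These round to the stated figures. Section 5.2.2.1 also says that the response-rate intervals in Table 4 are exact binomial. The protocol therefore handles rates by the binomial method everywhere except for DCR.

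**3. How far a Kaplan-Meier value could lie from the proportion.** The protocol gives neither an expected DCR nor a share of subjects without a post-baseline scan, so the following inputs are assumptions: n = 120 treated, C = 60 controlled, and U = 12, 18 or 24 unscanned (10%, 15%, 20%). The remaining n − C − U subjects progress at the first scan. The nearest Kaplan-Meier equivalent of DCR is the curve just after that scan.

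Target: C/n = 60/120 = 50.0%, exact 95% interval 40.7% to 59.3%.

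*All unscanned subjects count as events before the first scan:* [(n − U)/n] × [C/(n − U)] = C/n = 50.0%. The shift is 0 for any U.

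*All unscanned subjects are censored before the first scan:* C/(n − U).

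| Unscanned | Estimate | Shift |
|---|---|---|
| 10% (12) | 60/108 = 55.6% | +5.6 points |
| 15% (18) | 60/102 = 58.8% | +8.8 points |
| 20% (24) | 60/96 = 62.5% | +12.5 points |

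*Mixed case, 24 unscanned, 12 events and 12 censored:* if the censoring comes first, (96/108) × (60/96) = 60/108 = 55.6%. If the events come first, (108/120) × (60/96) = 56.3%. The shift is about 6 points.

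**4. Wider range, with all unscanned subjects censored.** For an assumed DCR of 30% to 50% and 5% to 25% unscanned, the shift runs from 1.6 points (36/114 against 36/120) to 16.7 points (60/90 against 60/120) at n = 120. At n = 41 it runs from 1.5 points (12/39 against 12/41) to 15.7 points (20/31 against 20/41).

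**The case against.** The case for leaving this alone is that little depends on it. DCR is an untested secondary endpoint. The go/no-go rule and the two-stage rule use response rate, and so does the primary analysis of the Expansion part. Section 15.2 also promises a general descriptive analysis of other anti-tumor activity, under which a proportion could be reported. All of that stands and sets the severity. It does not repair the sentence, because the general promise does not mention DCR and the only sentence that does names a method that cannot give it. Reading the entry as duration of disease control does not help either: no such endpoint is listed.

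A reader might go further and infer three things that the documents do not support.

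- *That the plan would censor unevaluable subjects and so inflate DCR.* No censoring rule for DCR is stated. Subjects who die before the first scan would probably count as events. The discontinuation scan would also give many early leavers a post-baseline assessment. It would not reach all of them, because someone who stops within 28 days of a screening scan may have none.
- *That Kaplan-Meier contradicts the inclusion of all treated subjects.* It does not. Censored subjects are still included in a Kaplan-Meier analysis, and PFS and OS in the same sentence rest on the same population.
- *That the figures in the table measure the harm of using Kaplan-Meier.* The same 60/108 arises from an ordinary proportion that leaves unscanned subjects out of the denominator. The shift reflects how missing assessments are handled, and the table shows its upper end.

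**Conclusion.** The point holds as a minor correction. The protocol specifies, in two places, an estimation method that does not fit a named secondary endpoint, and it makes that analysis conditional without need. This part rests on the text alone.

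The numerical consequence is uncertain. With 60 of 120 controlled and 10% to 20% unscanned, all assumed, it lies between 0 points and about 6 to 13 points upward, depending on whether unscanned subjects are treated as events or censored. With no unscanned subjects it is 0. The primary endpoint, the decision rules and the sample size do not change.

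**What to change.** Delete DCR from the Kaplan-Meier sentence in Section 15.2 and in the synopsis. Add in both places that DCR is reported as the number and percent of all treated subjects with disease control, with an exact binomial 95% confidence interval, and that subjects without a post-baseline assessment stay in the denominator as not controlled. The response categories that make up disease control can be set out in the statistical analysis plan.

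The cost is one sentence amended in two places. Data collection, trial conduct and sample size are unchanged.

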### **15.3. Background and Demographic Characteristics**

All analyses will be performed by study Phase and treatment group. The baseline characteristics of treated subjects will be summarized. An accounting will be made of all subjects who received investigational product(s) and, in particular, the number of subjects who died or withdrew during treatment will be specified together with the reasons for withdrawal.

#### **15.4. Investigational product(s)**

Descriptive summaries of investigational product(s) exposure will be provided by study Phase and treatment group.

#### **15.5. Safety Evaluation**

Data from all subjects who receive one or more doses of drug will be incorporated into the safety analyses. Investigational product(s) exposure will be summarized. Adverse events, vital sign measurements, clinical laboratory information, and concomitant medications will be tabulated and summarized by group and regimen. All toxicities will be summarized by relative and absolute frequency, severity grade based on the CTCAE version 4.0 and relationship to treatment. Serious adverse events (SAE) will be listed separately. Safety information obtained during the Follow-up period during each segment will be incorporated into these analyses. Graphical displays will be provided where useful in the interpretation of results.

#### **15.6. Interim Analyses**

There is no plan for interim analysis. However, Phase 2b – POC data will be analyzed and used to recommend the Phase 2b – Expansion part. The primary efficacy analysis will be based on Phase 2b – Expansion phase data alone.

#### **15.7. Sample Size and Power Considerations**

During Phase 2a – Safety Lead-in part, up to approximately 18 subjects will be enrolled.

In the Phase 2b – POC part, up to approximately 82 subjects will be randomized in a 1:1 ratio between lenalidomide in combination with cetuximab and lenalidomide alone. A Simon two stage minimax design will be used to monitor subject enrollment for each randomization arm separately. In the first stage, 23 subjects will be enrolled. If  $\leq 2$  of the 23 subjects ( $< 10\%$ ) have a response in either arm, the enrollment for that arm will be stopped. If  $> 2$  of the 23 subjects have a response in either arm, the enrollment in that arm will continue until 41 subjects are enrolled. If one arm is stopped, all new subjects will be enrolled in the remaining arm. At the final analysis, the regimen will be concluded with more than 10% true response rate if  $\geq 9$  of 41 subjects ( $>21\%$ ) have a response. This design will have 90% power to conclude the true response rate is higher than 10% at one-sided 2.5% level when the true response rate is 30%.

When any arm from the Phase 2b – POC is considered positive, the study may proceed with that regimen to the Phase 2b –Expansion phase. In the Expansion phase, approximately 120 subjects will be treated with the regimen. This sample size will allow for a two sided 95% confidence interval of (22%, 39%) when 30% response rate is observed.

## **16. QUALITY CONTROL AND QUALITY ASSURANCE**

### **16.1. Monitoring**

Celgene Corporation ensures that appropriate monitoring procedures are performed before, during and after the study. Before the study is initiated at a site visit or at an investigator meeting, all aspects of the study are reviewed with the investigator(s) and the staff. Prior to enrolling subjects into the study, a Celgene Corporation representative will review the protocol, CRFs, procedures for obtaining informed consent, record keeping, and reporting of AEs with the Investigator(s). Monitoring will include on-site visits with the Investigator(s) and his/her staff as well as any appropriate communications by mail, fax, or telephone. At each monitoring visit, the facilities, investigational product(s) storage area, CRFs, subject's source documents, and all other study documentation will be inspected/reviewed by the Celgene Corporation representative for adherence to the protocol and good clinical practice.

At each site visit, the monitor will review CRFs for completion and accuracy. Accuracy will be checked by performing source data verification that is a direct comparison of the entries made onto the CRF against the appropriate source documentation. Any resulting discrepancies will be reviewed with the Investigator(s) and/or his/her staff. Any necessary corrections will be made directly to the CRFs or via source data clarification forms by the Investigator(s) and/or his/her staff. Monitoring procedures require that informed consents, adherence to inclusion/exclusion criteria and documentation of SAEs and the proper recording be verified. Additional monitoring activities may be outlined in a study-specific monitoring plan.

